## Abstract

**Background:**

Major depression and depressive symptoms are common in patients with a recent myocardial infarction (MI), and depression is associated with adverse cardiovascular outcomes. Anxiety post-MI is less studied, but occurs commonly in patients with heart disease, and is also considered a risk factor for recurrence of cardiac events. Cognitive behavior therapy (CBT) is an established therapy for depression and anxiety disorders. To the best of our knowledge, there have not been any studies to determine if internet-based CBT (iCBT) can reduce the symptoms of depression and anxiety in patients with a recent MI. The main aim of the U-CARE Heart trial is to evaluate an iCBT intervention for patients with a recent MI.

**Methods/design:**

This is a randomized, controlled, prospective study with a multicenter design. A total of 500 participants will be randomized at a 1:1 ratio, around two months after an acute MI, to either iCBT or to a control group. Both groups will receive an optimal standard of care according to guidelines. The intervention consists of a self-help program delivered via the internet with individual online support from a psychologist. Treatment duration is 14 weeks. The primary outcome is change in patients’ self-rated anxiety and depression symptoms from baseline to end of treatment. An internal pilot study was conducted indicating sufficient levels of study acceptability and engagement in treatment.

**Discussion:**

The present study is designed to evaluate an iCBT intervention targeting symptoms of depression and anxiety in a post-MI population. If effective, iCBT has several advantages, and will potentially be implemented as an easily accessible treatment option added to modern standard of care.

**Trial registration:**

This trial was registered with Clinicaltrials.gov (identifier: NCT01504191) on 19 December 2011.

## Background

### Depression and anxiety is common in patients with myocardial infarction

Depression and depressive symptoms are common in patients with a recent myocardial infarction (MI). Major depression is reported to be prevalent in 20% of this patient population and, when including subsyndromal depressive symptoms, the prevalence is 31% [1]. Depression is also associated with adverse cardiovascular (CV) outcomes [2]. Furthermore, depression is a chronic, disabling condition associated with poor quality of life, functional limitation, less favorable self-care behaviors, and higher health care costs among patients with heart disease [3]. There are several possible mechanisms linking depression to cardiac events. Smoking and hypertension are known risk factors for heart disease that are more prevalent in depressed patients [4,5]. Depression is also associated with poor adherence to cardiac rehabilitation, which may lead to a less optimal recovery and worsened prognosis [6]. In addition, depression is an independent risk factor for future events. Possible mechanisms may be neuroendocrine dysfunction, disturbances in autonomic cardiac control, enhanced platelet activity, endothelial dysfunction, and inflammation [2].

Anxiety in patients with a recent MI and its association with prognosis has been less studied than depression, and the prevalence of patients diagnosed with anxiety is therefore uncertain. However, in one study, 38% of a post-MI group reported at least mild symptoms of anxiety, while only 18% in the same population reported at least mild symptoms of depression [7]. Importantly, in a large meta-analysis it was concluded that anxiety was not only common after MI, but also an independent risk factor for incident coronary heart disease and cardiac mortality [8]. Assumed mechanisms connecting anxiety and MI are more rapid progression of atherosclerosis, increased risk of ventricular arrhythmias, and unhealthier lifestyle factors, which are common among patients with anxiety and are known risk factors for heart disease [9]. Feelings of anxiety, sadness, and anger and/or hostility are highly correlated, and all are considered risk factors for first and recurrent cardiac events. It’s been suggested that at general disposition toward negative affectivity may be a more important risk factor than the expression of any specific negative affect [10].

### Psychological interventions for patients with a recent myocardial infarction

Psychological interventions may reduce the level of depression in cardiac patients according to a Cochrane review [11], and of the psychological interventions, cognitive behavioral therapy (CBT) has shown the most favorable results [12]. Despite the fact that anxiety is a risk factor for MI, very few treatment studies on anxiety in patients with a recent MI have been conducted [11]. To our knowledge, there is only one randomized controlled clinical trial (RCT), which showed no effect of the intervention [13]. There are several studies that have used group-based interventions focusing on a broader range of psychosocial risk factors with good results. These studies use CBT principles in a cognitive behavioral stress management program [14-16].

There is a high degree of spontaneous recovery of anxiety and depression in the first month after an MI [17]. By delaying the start of the treatment by two to three months after the acute event, one can exclude those who recover spontaneously from an initial depression or crisis and minimize the risk of treating people who will recover spontaneously. In the ENRICHD-study, therapy started two weeks after the MI, which led to substantial recovery in both the treatment group and the control group [18].

### Internet-based cognitive behavioral therapy

During the past decade, internet-delivered psychological interventions have become more common, and internet-based CBT (iCBT) has several advantages over traditional face-to-face CBT. First, the treatment can be delivered at any preferred time and place, and participants can work with the material at their own pace and review it as often as desired. Second, the level of therapist involvement can be adjusted and individualized; thus it may be possible to reduce the therapist time while maintaining efficacy [19]. Importantly, iCBT has been shown to be as effective as traditional CBT when it comes to anxiety and depression [19]. To achieve good compliance and results when delivering iCBT, individual support by psychologists is recommended [20]. It also seems beneficial to tailor the intervention towards specific problems in the target population instead of using generic treatments [21]. Although there are fewer studies available for iCBT, it seems to work well in populations with various somatic disorders [22]. To our knowledge, there are no RCTs available to determine the effects of iCBT in patients with a recent MI.

### Study objectives

The aim of the U-CARE Heart trial is to prospectively study the effects of iCBT in male and female patients with a recent MI with symptoms of depression and anxiety. Primary endpoints are change in self-rated depression and anxiety. Secondary endpoints are quality of life, stress behaviors, fatigue, sleep pattern, posttraumatic stress, and posttraumatic growth. Furthermore, we will evaluate health economy aspects and the cost-effectiveness of the intervention, and study its effect on later major adverse cardiac events.

## Methods/design

The present study is part of the Uppsala University Psychosocial Care Program (U-CARE), which aims at developing psychosocial care for somatic disease via the internet [23]. An internet platform (the U-CARE portal, Uppsala University, Uppsala, Sweden) has been developed within the U-CARE program. The U-CARE portal is used for data collection and interventions in all projects undertaken within the framework of the program.

### Study design and participants

U-CARE Heart is a prospective RCT. Figure 1 provides an outline of the trial design. A total of 500 participants will be recruited in a multicenter design, involving cardiology clinics in Sweden, in both rural and urban areas. Currently, 15 hospitals are engaged in the study. Inclusion and exclusion criteria are:

**Figure 1 Fig1:**
[figure not shown]
**U-CARE Heart overall study design.** HADS, Hospital Anxiety and Depression Scale; iCBT, internet-based cognitive behavioral therapy; MI, myocardial infarction.

Inclusion criteriaAge <75-years-old with a recent acute MI (<3 months)Depression and/or anxiety score of >7 on one or both of the Hospital Anxiety and Depression Scale (HADS) subscales [24].

Exclusion criteriaScheduled for a coronary artery bypass surgeryUnable or unwilling to use a computer or internet, including emailUnable or unwilling to use a mobile phoneDifficulties in reading or understanding SwedishLife expectancy of less than a yearAnticipated poor complianceHighly depressed or suicidal patients (Montgomery-Åsberg Depression Rating Scale Self Rating (MADRS-S) score >34 or MADRS-S item 9 > 3) [25]Participation in an ongoing trial with a behavioral intervention.

Participants scoring below eight on the HADS; will be allocated to a reference group which will be used to answer correlational research questions that are beyond the scope of this paper describing the RCT. Participants, both in the intervention group and in the control group, may seek other help such as psychopharmacology or counselling for their emotional problems if they wish to. Information on other treatment will be collected and controlled for in the statistical analyses. The first 20 randomized patients were included in an internal pilot study reported below. At that time of the pilot study, 12 hospitals were engaged in recruitment of participants.

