### Statistical power, sample size and statistical principles

We expect an effect size of the treatment on symptoms of depression and anxiety of at least Cohen’s *d* = 0.30 (a small effect size). This is based on the results from the ENRICHD study [18]. With α = 0.05 and a power of 90%, a sample of 468 participants is needed, of which 234 will receive the intervention. Main results will be analyzed according to the intention-to-treat principle and thus include all participants. When analyzing secondary outcomes, Holm-Bonferroni correction will compensate for multiple comparisons. The study is underpowered to detect a potential effect on major adverse cardiac events and these analyses will only be exploratory.

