### Standard of care

All patients in the study are treated medically according to international guidelines by the local health care system regardless of treatment allocation. Standard of care includes secondary preventive interventions and cardiac rehabilitation activities according to local routines. This includes education about the disease and of risk factors, encouragement for lifestyle behavioral changes (for example, smoking cessation, diet modification, and increased physical activity), and psychosocial support. Psychotropic medication may be prescribed if considered necessary.

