### Procedure

The patients are identified at the local hospitals one to eight weeks after their MI. The patients are contacted by project personnel 8 to 12 weeks after their MI and are sent an informed consent form for signing. After returning the signed consent form they are provided with login details. Each participant receives a username and password that they can change at their own choice. At each session they will also receive a text message with a five-digit numerical password to enter, in order to enhance security. Patients with signs of severe depression or reporting suicidal ideation when answering the baseline assessments will be excluded from the study and contacted via telephone by a project psychologist and, if needed, referred to adequate treatment. Likewise, if there is reason to believe that they have developed severe depression or have become suicidal during the study, patients will be contacted by the psychologist for assessment and possibly referred to other treatment. Reminders via email and text messages will be sent automatically from the platform if the questionnaires are not completed within seven days, and by telephone if they still have not been completed after another seven days.

The status of depression and/or anxiety for those in treatment will be monitored by the therapist via communication within the portal. If there are any indications of suicidal ideations or worsening of symptoms the therapist will contact the participant by telephone to evaluate their status, give advice on how to obtain other treatment or encourage them to carry on with their iCBT program.

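### The protocol commits, without restriction, to controlling for other treatment; as worded this reaches treatment started after randomisation and would not estimate the intention-to-treat effect

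*Protocol article*

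**What the plan says.** Under Study design and participants, after the exclusion criteria, the protocol says that participants in either arm "may seek other help such as psychopharmacology or counselling for their emotional problems if they wish to". The next sentence is "Information on other treatment will be collected and controlled for in the statistical analyses". It names no model, no time of measurement and no class of outcome.

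Four other statements bear on it.

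- Statistical power, sample size and statistical principles: "Main results will be analyzed according to the intention-to-treat principle and thus include all participants".
- Standard of care, which applies in both arms, includes psychosocial support, and "Psychotropic medication may be prescribed if considered necessary".
- Procedure: "The status of depression and/or anxiety for those in treatment will be monitored by the therapist via communication within the portal". If there are signs of suicidal ideation or worsening, the therapist telephones to assess the participant and to "give advice on how to obtain other treatment or encourage them to carry on with their iCBT program".
- Abstract, Methods/design: "The primary outcome is change in patients’ self-rated anxiety and depression symptoms from baseline to end of treatment". Treatment lasts 14 weeks, so there is time for other treatment to start between randomisation and the primary assessment.

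**The concern.** The sentence on adjustment follows directly on one about people already in the intervention or control group, so its natural reading is help sought during the trial. That is a post-randomisation variable with two awkward properties. It is driven by emotional symptoms, which HADS measures as the main outcome. It can also be changed by allocation: effective iCBT may reduce the need for other help, while the therapist contact described for those in treatment may prompt it.

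A regression that holds such a variable fixed can remove part of the total effect (the variable acts as a mediator). It can also create a difference between arms that treatment did not cause (the variable acts as a collider between arm and underlying distress). Medication and psychosocial support belong to the standard care to which iCBT is added, so their uptake is part of the effect the trial sets out to measure. Keeping every participant in the analysis does not repair this.

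At stake is the meaning of the treatment coefficient in any model to which the sentence is applied. If the wording is left open, there is also the freedom to choose that model after uptake by arm is known.

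**Working it through.** **1. The plan's own figure.** Inputs from the sample-size section: d = 0.30, α = 0.05 (taken as two-sided), power 90%, 1:1 allocation.

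n per arm = 2(z₀.₉₇₅ + z₀.₉₀)² / d² = 2(1.960 + 1.282)² / 0.09 = 233.5, so 234 per arm and 468 in total. This reproduces the protocol and is not in dispute.

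**2. What adjustment does to the estimate.** Let M be an indicator of other treatment after randomisation. In a linear model with arm and M,

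adjusted effect = unadjusted effect − γ × (p_iCBT − p_control),

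where γ is the coefficient of M and the p are the proportions using other treatment. The departure is zero if use is equal across arms or if γ is zero. Otherwise its sign depends on both factors.

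**3. Illustration.** The documents give no value for γ or for the proportions, so every input below is an assumption. Simulations used 2 million patients per scenario, outcome SD about 1, lower scores better, and a true total effect of −0.30 SD. Underlying distress enters the outcome with coefficient 0.5. Its correlation with the tendency to seek help is 0 or 0.5, as shown. Unadjusted effects differ from −0.30 only by simulation error.

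| Use, control v iCBT | Distress–help correlation | Effect of other treatment (SD) | γ | Unadjusted | −γ × difference in use | Adjusted |
|---|---|---|---|---|---|---|
| 20% v 20% | 0.5 | 0 | 0.441 | −0.301 | 0 | −0.301 |
| 30% v 15% | 0 | −0.4 | −0.401 | −0.298 | −0.060 | −0.359 |
| 30% v 15% | 0.5 | 0 | 0.428 | −0.301 | +0.064 | −0.236 |
| 30% v 15% | 0.5 | −0.4 | 0.030 | −0.297 | +0.005 | −0.292 |
| 30% v 10% | 0 | −0.4 | −0.402 | −0.297 | −0.080 | −0.377 |
| 30% v 10% | 0.5 | 0 | 0.436 | −0.301 | +0.087 | −0.214 |
| 15% v 25% | 0 | −0.4 | −0.399 | −0.302 | +0.040 | −0.262 |
| 15% v 25% | 0.5 | 0 | 0.437 | −0.297 | −0.044 | −0.341 |

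With no shared cause, the adjusted value is the direct effect, which is a different quantity from the total effect. With a shared cause and an inert other treatment, direct and total effects are both −0.30, yet the adjusted value is −0.236 or −0.214 with lower use under iCBT and −0.341 with higher use: pure selection bias. The two mechanisms can also nearly cancel (fourth row).

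Two further simulations with other assumed inputs gave adjusted effects of 0.24 to 0.32 and of 0.28 to 0.33 SD, against a true 0.30.

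**4. True null.** The departure −γ × (difference in use) does not contain the treatment effect. The same shifts therefore appear when the total effect is zero, provided that use still differs by arm: in this table, up to 0.080 SD in favour of iCBT and 0.087 SD in favour of control. The standard error with 234 per arm and SD 1 is √(2/234) = 0.092. A shift of 0.02 SD then gives about 5.5% two-sided rejection, and 0.06 SD about 10%.

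**5. Power, like for like.** Power = Φ(d√(234/2)/s − 1.96), with s the residual SD.

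- Unadjusted (s = 1): at 0.24, Φ(2.596 − 1.96) = 74%, against 90% at 0.30.
- Adjusted for baseline, assuming a baseline–outcome correlation of 0.4 to 0.6 (s = 0.917 to 0.80): 81% to 90% at 0.24, against 94% to 98% at 0.30.

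**The case against.** The sentence does not name the primary analysis, a regression covariate or the time at which other treatment is measured. Self-reports are taken at baseline, 14 weeks and 12 months, so treatment in use at baseline could be what is meant, and adjusting for that is legitimate. An analysis plan that is not shown may say so. This stands as a limit on certainty: a reader might infer that the primary estimate is already something other than the intention-to-treat effect, and the document does not establish that. It does not remove the point, because the text is an unrestricted commitment and no other section narrows it.

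A reader might also infer a flat contradiction with the intention-to-treat statement. The protocol explains that principle only as including everyone, and a covariate does not breach it in that sense. The conflict is with the usual meaning, the effect of allocation whatever treatment follows.

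Nor does the Procedure section show that iCBT therapists routinely direct participants to other treatment. The advice is conditional on worsening or suicidal ideation, and encouragement to continue iCBT is the stated alternative. The same section also provides, for all participants, psychologist contact and possible referral if severe depression or suicidality develops. What remains specific to iCBT is the regular therapist monitoring. A difference between arms is therefore plausible, but its size is undocumented.

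Finally, a fall in power from 90% to 74% is tempting to quote. It is an unadjusted figure for one unfavourable scenario and should not be given as a forecast for a baseline-adjusted analysis.

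**Conclusion.** The point holds as one about wording that permits, and read naturally prescribes, an unsuitable adjustment. Conditioning on treatment started after randomisation would not estimate the intention-to-treat effect of adding iCBT to standard care.

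Size and direction cannot be derived from the documents. Under the assumed inputs the departure is about zero with equal use and otherwise a few hundredths of an SD, at most about 0.09 SD, in either direction, including under a true null. The tabled scenarios leave baseline HADS out of the model; including it could absorb part of the shared distress and so change γ. The planned 468 is unaffected. The principle is certain; what the primary model will contain is not.

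**What to change.** Replace the sentence so that it states three things:

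- Primary and secondary comparisons between randomised arms adjust only for variables measured before randomisation: baseline HADS, centre (the stratification factor) and, if wanted, treatment already in use at baseline.
- Other treatment during the trial is reported descriptively by arm.
- Any analysis that accounts for treatment started after randomisation is supplementary, labelled as such, with its target quantity and assumptions stated.

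This should be settled before uptake by arm is examined. The cost is one sentence in the protocol and the matching text in the analysis plan. Data collection, sample size and patient care stay as they are.

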### Statistical power, sample size and statistical principles

We expect an effect size of the treatment on symptoms of depression and anxiety of at least Cohen’s *d* = 0.30 (a small effect size). This is based on the results from the ENRICHD study [18]. With α = 0.05 and a power of 90%, a sample of 468 participants is needed, of which 234 will receive the intervention. Main results will be analyzed according to the intention-to-treat principle and thus include all participants. When analyzing secondary outcomes, Holm-Bonferroni correction will compensate for multiple comparisons. The study is underpowered to detect a potential effect on major adverse cardiac events and these analyses will only be exploratory.

### Randomization

Participants will be randomized (1:1) to either iCBT or standard of care. Randomization will be stratified by clinical center to obtain approximately equal sample sizes in both groups from every center.

### The internet-based cognitive behavioral therapy intervention

The iCBT intervention is inspired by face-to face CBT for psychological problems and earlier iCBT-manuals. CBT is a short-term therapy that aims at challenging negative patterns of cognitions and behaviors leading to negative feelings. It usually contains self-registrations and introduction of new, more functional, cognitions or behaviors. The iCBT intervention starts with a general introduction to the CBT model. The participants are asked to describe their present concerns and goals with their participation in the treatment. After completing the introduction, the participants will, with help from their therapist, choose the problem area(s) they want to work with. This self-tailored design is suggested to give the participants more control while maintaining treatment quality [26]. There are 10 treatment modules to choose from in the portal Each participant chooses two or three of the modules below after finishing the mandatory introduction to cognitive behavioral therapy:Worry managementFear and avoidance after a myocardial infarctionBehavioral activationProblem solvingCommunication trainingRelaxationCognitive restructuringCoping with insomniaValues in lifeRelapse prevention.

Each module contains two to four steps, and the participants are suggested to work with one step each week, for a total of 14 weeks. The treatment program includes texts, presentations, assignments, and self-monitoring, and offers a weekly feedback from a psychologist over the internet. The content of the modules were designed specifically for this study.

In addition, the participant can communicate with their psychologist through the portal at any time and ask for support or clarifications. Participants who do not log in or follow the treatment plan are reminded via automatic emails, text messages, telephone calls, or postal mail at their choice and are encouraged to continue.

The U-CARE portal also contains a discussion forum where participants have the possibility to communicate with each other, as well as videos with patients who have had an MI and who have struggled with negative feelings afterwards.

